**11.** **Safety Assessment**

Patients remain in contact with the Center's staff, having received the medication under supervision and being evaluated in conjunction with each of the blood samples. A doctor will be available throughout the study at any time.

***11.1.*** ***Tolerance variables***

An evaluation of all adverse events reported by patients or observed by the research team, including abnormal laboratory findings.

Each volunteer will be asked in general: Do you see any difference in your physical condition from the previous to the administration of the drug?, Coinciding with each blood sample. Any AA referred spontaneously or as a result of the research question will be recorded in the medical record of the volunteer, specifying the time of onset, course, duration, intensity, necessary treatment and medication relationship. Upon completion of the survey will be repeated physical examination and laboratory tests each volunteer.

*11.1.1.*     *Definition of an adverse event*

An AE is any undesirable experience occurring or worsening during the course of the study, regardless of causal relationship to study medication. In addition, all events occurring in connection with the study before or after the clinical period, ie between the screening visit and the visit of final review, must be valued as an AA. Adverse events are not considered drowsiness, sedation, gait instability or standing, but its appearance is collected in the same manner as other adverse events.

The following effects are classified as AA:

Worsening (change in the nature, intensity or frequency) of the conditions at baseline.

Deterioration of the subject due to primary disease.

Intercurrent disease.

Drug Interactions.

Events related or possibly related to concomitant medication.

Significant abnormal laboratory values ​​and significant deviations from the reference values, but within the normal range, which the investigator considered clinically important.

The AA will be recorded on a sheet of AA history and classified as mild, moderate or severe, according to the following definition:

Minor: not cause limitation of usual activities. The subject may experience a slight discomfort.

Moderate : cause some limitation of usual activities. The subject may experience discomfort.

Severe : inability to perform usual activities. The subject may experience intolerance, discomfort or pain.

A grave is a AA AA is:

Fatal.

Threatening to life.

Produce permanent disability.

subject requires hospitalization or prolongation of the same.

Produce congenital anomaly.

Cancer.

Overdose or intoxication.

Any AA that, in the opinion of the investigator, is considered serious and is not covered by the above.

An unexpected AA experience is defined as described not in terms of nature, severity or frequency in the investigator's brochure ..

*11.1.2.*     *Defining an adverse event causality*

The investigator will determine the relationship of any AA with study medication according to the following criteria (according to "Modified to the classification of Karch / Lasagna, Journal of the American Medical Association 234:1236-1241, 1975"):

*Short* : the reaction is with a reasonable time sequence after drug administration. The effect had previously been referred to or is an expected response to the study drug, confirming an improvement after the reduction or suspension of the drug and recurrence of effect after readministration of the same, with no apparent alternative etiology.

*Probable* : Reaction appears reasonable time sequence after drug administration. The effect has already been referred to previously or is an expected response to the study drug. Improvement occurs after reduction or discontinuation of treatment, and any other etiology is unlikely or less likely.

*Possible* : The reaction appears reasonable time sequence after drug administration. The effect had previously been referred to or is an expected response to the study drug. There is a possible alternative that may be responsible etiological AA.

*Unlikely* : the reaction does not appear with a time sequence after drug administration, or if exists, it is remote. The effect is not an expected response, or known to the study drug. There is a possible alternative that may be responsible etiological AA.

*Unrelated* : the AA is due to an underlying disease or concurrent or the effect of another drug and is not related to study medication (not to be related temporary or most likely alternatives exist).

The parameters of clinical and laboratory tolerance will be evaluated descriptively and differences using a Student t test (paired data), indicating hematological and biochemical parameters (See Annex IV for reference values) and BP, HR, RR and T ª, will be discussed and AA abnormal values. If any abnormality is observed, will convene again to volunteer to repeat this determination and this will be followed up until all changes are considered as clinically relevant.

*11.1.3.*     *Procedures for recording adverse events*

All AA that occur during administration of study treatment, either spontaneously reported by the subjects or observed by the investigator, are (in the opinion of the investigator) related or not, must be picked up in the history and transcribed the AA page contained in the CRD. The researcher also determined the relationship between AA and study drugs and recorded in the appropriate section of the notebook.

*11.1.4.*     *Notification of adverse events*

The researcher informed all AA promoter that occur during the study, regardless of their relationship to the study drugs.

A serious or unexpected AA or not related to study medication ICT must be informed within 24 hours of becoming aware of it.

After disclosure, the investigator shall complete and sign a report for the written notification to the promoter.

The researcher, as delegated by the Promoter, communicate to the competent authority within the AA up to 7 days in the case of AA involving fatal or life-threatening (those not been for immediate therapeutic intervention would have meant the death of the patient ). If not had all the information it can be completed within an additional 8 days. Other unexpected serious AEs be reported within 15 days.

Reports on the course which the subject in relation to the AA should be made until it is gone or the clinical situation has stabilized and presented to the developer. If required, additional information will be provided.

It is the responsibility of the Promoter AA reporting serious and unexpected to the Clinical Research Ethics Committee, the Spanish Agency for Medicines and Health Products and Pharmacovigilance Center of Navarre. On the relationship between developer and researcher, the first delegates to the researcher communicating these AA to health authorities and CEIC.

**12.** **STATISTICS**

***12.1.*** ***Statistical methods***

The pharmacokinetic and statistical analysis of the data will be performed by UIC in the University Clinic of Navarra.

Pharmacokinetic analysis was performed on the data of concentrations of all evaluable volunteers completed the study as set forth in the protocol: pharmacokinetic profile with both formulations. The following pharmacokinetic parameters of palonosetron, will be determined for each subject following administration of each treatment:

-Cmax = maximum concentration,

-AUC _0-t_ = area under the curve versus time to the last quantifiable sample (time t), calculated using the trapezoidal method.

-Tmax = time of Cmax is reached,

-The elimination half-life, t _1/2_ , will be determined by the following expression:

t _½_ = ln 2 / k _e_

There will be a descriptive analysis of palonosetron pharmacokinetic parameters after subcutaneous administration.

Bioavailability is calculated in this way by calculating the ratio of AUC _0-t_ obtained after subcutaneous and intravenous administration.

Other parameters (analytical data, blood pressure) were analyzed using Student t test for paired data or ANOVA as appropriate, after having determined that the conditions for applying these tests. In the case of non compliance will be analyzed using appropriate nonparametric tests (Wilcoxon, Friedman).

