**14. - Study population and number of volunteers.**

Cancer patients undergoing chemotherapy emetic. Will include a minimum of 25 evaluable patients (with pharmacokinetic evaluation SC and IV administration).

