***7.6.*** ***Withdrawals and replacements***

Volunteers will be excluded from the study at their own request or by decision of the investigator when either of the following reasons:

intercurrent disease or AA if intolerable.

Violation of the foregoing restrictions.

Volunteer personal reasons for not continuing in the study.

Excluded subjects who leave the study for any of the above reasons will be replaced, to have a number of 25 evaluable patients, with complete pharmacokinetics of both routes of administration.

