**9.** **ASSAY DEVELOPMENT**

***9.1.*** ***Study Plan***

*9.1.1.*        *Selection stage*

In the 20 days before the start of the intervention phase of the study will be the selection of volunteers. This phase will recruit 25 patients will be informed of the design, objectives and possible risks of the study. Each patient will have the opportunity to ask any questions you want to research. Before any test is obtained written informed consent.

They perform a complete medical history that includes:

• Detailed anamnesis.

• Complete physical examination with assessment of functional status (ECOG scale).

• Registration of drugs administered to the patient at the time of inclusion.

• Laboratory tests:

Hematology: CBC.

Biochemistry: blood: cre atinina, urea, SGOT (AST), SGPT (ALT), GGT, total bilirubin, electrolytes

In case the patient has already been subjected to this analysis in the 10 days prior to administration of the medication can not be repeated.

With all these data verify the eligibility of patients to participate in the study.

*9.1.2.*        *Intervention phase*

The intervention phase will consist of two periods in which the patient will receive the study medication. Each will have a minimum duration of 12 hours, separated by at least two weeks washout period. In each volunteer will receive a dose of palonosetron 250 μ g intravenously or subcutaneously, according to the randomization code. Before the second administration of the drug is verify that the patient has adequate hepatic and renal function.

Will place a peripheral venous independent pathway by the patient receive chemotherapy and palonosetron, through which the blood samples drawn for determination of the drug.

They undertake every single day of intervention:

- Determination of the SBP and DBP, FC and temperature in a sitting position before administration of the study medication.

Blood drawn at baseline (5 ml).

Assessment of pain by visual analog scale.

After drug administration was performed:

Blood samples (5 ml) at the following times: end of infusion, 10 - 15 - 30 - 45 - 60 mins, 1,5 - 2 - 3 - 4 -8 to 12 hours. If income permits 24 hours.

Collection of urine during the 12 hours of study.

Subjective assessment of pain using a visual analog scale at the time: 1 to 4 and 8 hours.

Physical examination of the administration at 1, 4 and 8 hours after administration.

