***13.9.*** ***Withdrawal from the study***

Volunteers will be informed that they can withdraw at any time. This removal may occur by any of the following reasons:

Will the participant.

Significant breach protocol.

Intercurrent disease that interferes with the development of the study.

Occurrence of adverse events or other situations that, in the opinion of the investigator, pose a risk to the volunteer.

Appearance of exclusion criteria for the study

The withdrawal will be documented in the medical record, stating the reasons. Should be conducted, as far as possible, a final review visit when you have received at least one of the study medications.

He will replace retired volunteers, if is compromised the validity of the study, ie the number of evaluable volunteers is less than 25.

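### Section 12.1 limits every pharmacokinetic analysis to patients with both routes, so valid subcutaneous profiles from sc-first patients who leave are dropped from a description that needs only the sc profile (minor)

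*Protocol*

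**What the plan says.** Section 12.1 opens the pharmacokinetic analysis with its population: "Pharmacokinetic analysis was performed on the data of concentrations of all evaluable volunteers completed the study as set forth in the protocol", followed by the gloss "pharmacokinetic profile with both formulations". Two analyses then follow, neither with a population of its own. One is descriptive: "There will be a descriptive analysis of palonosetron pharmacokinetic parameters after subcutaneous administration". The other is bioavailability, the ratio of sc to iv AUC0-t.

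Other sections agree on what evaluable means. Summary item 14: "Will include a minimum of 25 evaluable patients (with pharmacokinetic evaluation SC and IV administration". Section 7.6 says that patients who leave "will be replaced, to have a number of 25 evaluable patients, with complete pharmacokinetics of both routes of administration". Section 13.9 replaces withdrawn patients when validity is compromised, "ie the number of evaluable volunteers is less than 25".

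The listed reasons for leaving include "intercurrent disease or AA if intolerable" (7.6). Section 13.9 adds the appearance of an exclusion criterion. Before cycle 2 there is also a check: "Before the second administration of the drug is verify that the patient has adequate hepatic and renal function" (9.1.2). No section keeps the sc profile of a patient who had sc first and did not reach cycle 2.

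**The concern.** The two analyses need different data. A within-patient ratio needs both profiles. A summary of sc Cmax, tmax, AUC0-t and half-life needs only the sc profile. The sc summary is not a side product: Summary item 10 makes sc pharmacokinetics the main objective, Summary item 13 and section 10.1 list these exposure parameters as primary, and section 7.1 justifies 25 patients as enough to describe sc pharmacokinetics, with bioavailability included. The population that suits the ratio is therefore imposed on the broader description.

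Two things are at stake. Usable data are discarded after the patient has been dosed and sampled for 12 hours. And because some reasons for leaving concern health or tolerability, the patients described may differ from those dosed. Replacement brings the count back to 25 but does not address that second point.

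**Working it through.** **Stated figure.** The protocol chooses 25 by judgement (7.1), with no formula, variance or dropout rate, so there is nothing to reproduce.

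**Inputs.**
- Patients with both profiles: 25 (Summary item 14, sections 7.1 and 7.6).
- Fraction *d* leaving between cycles: not given; assumed 10%, 20% and 30%.
- Sequence split: two sequences (6.2), ratio not stated in the text; assumed equal, with equal dropout in both.
- Spread of sc values: assumed the same in leavers and completers.

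**Formulas.**
- Patients dosed in cycle 1: N = 25/(1 − d).
- Sc profiles discarded: x = (N − 25)/2, since only sc-first leavers have one.
- Standard error with these profiles kept, relative to 25 profiles: √(25/(25 + x)).
- Share of the enlarged sc set that comes from leavers: f = x/(25 + x).

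| d | N | x | SE ratio | f |
|---|---|---|---|---|
| 10% | 25/0.9 = 27.8 | 2.8/2 = 1.4 | √(25/26.4) = 0.973 | 5.3% |
| 20% | 25/0.8 = 31.25 | 6.25/2 = 3.1 | √(25/28.1) = 0.943 | 11.1% |
| 30% | 25/0.7 = 35.7 | 10.7/2 = 5.4 | √(25/30.4) = 0.907 | 17.6% |

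The standard error falls by about 3%, 6% and 9%. Rounding N up to 28, 32 and 36 whole patients gives 1.5, 3.5 and 5.5 discarded profiles, which is the same picture.

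**Possible selection, as illustration only.** Suppose sc-first leavers had mean sc exposure *r* times that of completers. The completer mean then differs from the mean over all sc profiles by 1/(1 + f(r − 1)) − 1. The protocol gives no basis for *r*; the values 0.8 and 1.5 are assumptions.

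| d | r = 0.8 | r = 1.5 |
|---|---|---|
| 10% | 1/0.9895 − 1 = +1.1% | 1/1.026 − 1 = −2.6% |
| 20% | 1/0.978 − 1 = +2.3% | 1/1.056 − 1 = −5.3% |
| 30% | 1/0.965 − 1 = +3.7% | 1/1.088 − 1 = −8.1% |

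The sign depends on *r*, so no direction can be stated.

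**Scale.** The table in section 4.1.2 gives CVs of 44% and 61% for iv Cmax at 0.25 mg. If sc were similar, the standard error of the mean with 25 patients would be 44%/√25 = 8.8% to 61%/√25 = 12.2%. The illustrated shifts are smaller than this.

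**What the change leaves untouched.** With the discarded profiles kept, leavers make up 5.3%, 11.1% or 17.6% of the sc set, against 10%, 20% or 30% of those dosed in cycle 1. The rest are iv-first leavers, who never have an sc profile. The sc set also becomes slightly unbalanced: if completers split equally, it holds N/2 = 13.9, 15.6 or 17.9 sc-first patients against 12.5 iv-first.

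**The case against.** The case for leaving the text alone is substantial.

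- Section 5.1 frames the primary objective as sc absorption compared with iv. One paired set keeps the sc summary, the iv summary and the ratio consistent with each other. This stands as a reason to keep the both-routes description, but not to make it the only one.
- The study is called a pilot (6.1), the sc analysis is descriptive with no decision threshold, and replacement restores the planned 25. A reader might infer that the rule takes precision away from the plan. It does not; it forgoes a small gain.
- A reader might also infer that the patients described are healthier than those treated. The documents do not show this. Leaving may also be for personal reasons or for breach of restrictions (7.6), the first profile is complete within 12 hours (24 if the admission allows), and nothing links later withdrawal to sc uptake. Section 4.1.2 reports no change in pharmacokinetics in the elderly or in renal or liver failure. That concerns parenteral disposition, and section 6.4 says no sc absorption data exist, so it tempers the concern without settling it.
- Safety information is not lost: adverse events are recorded for all patients (11.1), and section 13.9 seeks a final visit after at least one dose.

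What remains is that valid sc profiles are excluded from an analysis that does not need the second route. An analysis plan was not available, but the protocol itself fixes this rule, so it is not a detail left open.

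**Conclusion.** The point holds, at minor severity. Section 12.1, read with Summary item 14 and section 7.6, drops the sc profiles of sc-first leavers from the descriptive sc analysis without need. For the sc/iv ratio the both-routes set is appropriate and should stay.

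The loss is about 1.4, 3.1 or 5.4 profiles, and the forgone reduction in standard error about 3%, 6% or 9%, at assumed dropout of 10%, 20% or 30% with equal sequences. Some selection is possible because some withdrawals are health-related, but its direction and size are unknown. A reader might conclude that keeping these profiles would remove the selection. It would not, since every sc profile from an iv-first patient still depends on reaching cycle 2.

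**What to change.** Reword section 12.1 so that:

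- Cmax, tmax, AUC0-t and half-life are described, for each route, in every patient with an adequate profile for that route;
- the paired sc/iv ratio of AUC0-t uses only patients with both profiles;
- the both-routes description of each route is shown alongside, with the number of patients and the sequence split for each set.

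The target of 25 patients with both profiles and the replacement rule can stay.

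The cost is wording and one more table. No new samples, visits or patients are needed, and the ratio is unaffected. The small downside is that the sc and iv summaries come from slightly different patients and the sc set is slightly unbalanced by sequence. The side-by-side table deals with this and lets the reader see whether the two descriptions differ.

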***4.1.*** ***Pharmacological aspects***

Antagonists 5-HT _3_ receptors are a family of important antiemetics to prevent emesis induced by cytostatic high emetogenic as cisplatin and lack of antidopaminergic activity. Have identified a range of different chemical structures with anti-5-HT3 receptors (ondansetron, granisetron, tropisetron, dolasetron, palonosetron etc ...). The differences between them lie in the chemical structure and the pharmacokinetic behavior, and its levels of effectiveness and side effect profile quite similar.

Currently antagonists 5-HT _3_ receptors are used as first line treatment in virtually all patients who receive highly emetogenic chemotherapy regimens (platinum regimens containing anthracyclines or other cytostatic high dose) in patients expected the emergence of side effects with metoclopramide or in those with inadequate response to previous treatment.

Palonosetron is an antiemetic agent, serotonin antagonist with high affinity for the 5HT _3_ receptor. It is the most potent antagonist in the treatment group. Prevents the occurrence of vomiting with a power between 2 and 93 times higher than that observed with ondansetron or granisetron.

*4.1.1.*        *Clinical Use*

Palonosetron is indicated for the prevention of acute nausea and vomiting associated with cancer chemotherapy moderately and highly emetogenic.

*4.1.2.*        *Pharmacokinetics*

Pharmacokinetics of palonosetron have been evaluated when administered parenterally. Bioavailability is not known in other ways.

Plonosetron shows linear kinetics μ between 0.3 and 90 g / kg (Eisenberg 2004).

It is widely distributed in the body, presenting a volume of distribution of 6.9 to 7, 9 l / kg (Sloltz 2004). The plasma protein binding is not high, about 62%.

The 40% of the administered drug is excreted in urine, 50% is converted by hepatic metabolism, mainly by the liver microsomal system. Mainly involved in the metabolism isoenzymes CYP2D6 and to a lesser extent, CYP3A4 and CYP1A2. Despite this involvement of cytochrome, has not been observed that the genetic polymorphism affecting the elimination of palonosetron.

The half-life of palonosetron is about 40 hours with a total clearance of 173 ml / min and the renal 53 ml / minute.

No change was observed in the pharmacokinetics in the elderly, renal or liver failure.

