Palonosetron did not inhibit or induce cytochrome CYPP450. Nor has any suffered no interaction with drugs, inhibitors or inducers, administered concomitantly.

| **Pharmacokinetic parameters** | **Mean (CV)**  **n = 12** | **Mean (CV)**  **n = 11** | **Mean (**± **SD)**  **n = 11** |
| --- | --- | --- | --- |
|  | Hunt 2005 | Shah 2006 | Eisenberg 2004 |
| ***Dose mg*** | 0.25 | 0.25 | 3 μ g / kg |
| ***Infusion time (seconds)*** | 10 | 15 | 30 |
| ***AUC*** ***_0-24_*** **(ng** × **h / l)** | 8,900 (22%) | - | ± 8.570 4.220 |
| ***AUC*** ***_0 -_*** *_∞_* **(ng** × **h / l)** | - | 20,700 (25%) | ± 35,800 20,900 |
| ***Cmax*** **(ng / l)** | 1,130 (61%) | 919 (44%) | ± 5.630 5.480 |
| ***t*** ***_1/2_*** **(h)** | 42.8 (25%) | 37 (24%) | 56.4 ± 5.8 |

*4.1.3.*        *Adverse Reactions*

Palonosetron, a single dose administered before chemotherapy is well tolerated in general (Siddiqui 2004):

Side effects reported most often in connection with the administration of palonosetron were headache (9%) and constipation (5%).

*4.1.4.*        *Precautions*

Use cautiously in patients with constipation or signs of intestinal obstruction, because I could make symptoms worse.

Although no ECG changes observed with palonosetron, caution should extermarse when used concomitantly with drugs that prolong the QT interval of the ECG, as is done with other 5-HT _3_ antagonists.

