***9.2.*** ***Handling of blood samples***

*9.2.1.*        *Extractions*

After administration of palonosetron, there will be blood samples (5 ml) at the following times: end of infusion, 10 - 15 - 30 - 45 - 60 mins, 1,5 - 2 - 3 - 4 -8 to 12 hours. If income permits 24 hours.

Blood will be drawn from the vein. EDTA tubes are used (5 ml).

Samples were centrifuged at 3500 rpm for 10 minutes at 4 ° C within 30 minutes after removal. The resulting plasma was separated into two aliquots for determination of palonosetron, and freeze at -70 ° C until shipment to the laboratory for analysis. Palonosetron determining aliquots of plasma will be by high resolution liquid chromatography with mass spectrometer detection (LC / MS). The conditions of sample handling can be modified depending on the analysis technique, which is in development.

*9.2.2.*        *Labelling*

Samples for the determination of palonosetron is labeled with the following information:

-           Line 1:               Name of the active ingredient (palonosetron).

-           Line 2:               study identification code. Route of administration. Aliquot (original or duplicate).

-           Line 3:               Number of subject randomization. Initials. Period administration.

-           Line 4:               The time of extraction.

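### Section 12.1 promises an elimination half-life for each patient and route, which required sampling to 12 h (24 h only if the stay permits) cannot support when the half-life is about 40 h

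*Protocol*

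**What the plan says.** Section 12.1 lists the parameters that "will be determined for each subject following administration of each treatment". They are Cmax, AUC0-t, tmax and half-life. For the last it says "The elimination half-life, t _1/2_ , will be determined by the following expression", and the expression is ln 2 divided by ke. It does not say which samples give ke, or what happens when no terminal phase is seen.

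Section 4.1.2 says "The half-life of palonosetron is about 40 hours", and section 9.3 uses the same figure to justify the washout. The table in section 4.1 gives half-lives of "42.8 (25%) | 37 (24%) | 56.4 ± 5.8" h from three cited studies.

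Sections 9.1.2 and 9.2.1 set the late samples as "3 - 4 -8 to 12 hours. If income permits 24 hours". Section 4.2 plans a 12 h stay. Section 6.4 says the times were chosen to locate tmax and cover absorption, and that sampling is deliberately not extended. Section 10.1 names only Cmax, AUC0-t and tmax as primary.

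**The concern.** The sampling schedule was built for absorption, yet section 12.1 commits to an elimination parameter. The required samples cover under a third of one half-life, and the last three required points span 8 h, or 0.2 of one. Two things can go wrong. Concentrations fall so little over that span that assay error can swamp the slope. And if the drug is still distributing, or still being absorbed after subcutaneous dosing, the slope is not the elimination slope at all.

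At stake is a published half-life that could be far from the truth or undefined in some patients. Patients with and without the 24 h sample would also have values from different windows, which should not be pooled as one parameter.

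**Working it through.** **1. The protocol's own half-life.** The n-weighted mean of the two 0.25 mg studies is (12 × 42.8 + 11 × 37)/23 = 40.0 h, which agrees with "The half-life of palonosetron is about 40 hours". As a second check, use ln 2 × V / CL with CL = 173 ml/min = 10.38 L/h and V = 6.9–7.9 L/kg. This gives 32–37 h at an assumed 70 kg and 37–42 h at 80 kg. The 40 h figure is sound.

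**2. How much of it is sampled.** 12/40 = 0.30 half-lives; across the table's 37–56.4 h this is 0.32–0.21. With the conditional sample, 24/40 = 0.60. At 40 h the expected fall from 4 to 12 h is 1 − 2^(−8/40) = 13%, and from 8 to 12 h it is 1 − 2^(−4/40) = 6.7%.

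**3. Precision with no bias at all.** Assume a pure mono-exponential decline and log-linear regression. The protocol gives no assay precision (section 9.2.1 says the method is in development), so proportional errors of 5% and 10% are assumed.

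SE(slope) = CV / √Σ(t − t̄)². The probability of a non-positive slope is Φ(−ke/SE). ke = ln 2/40 = 0.0173 per h.

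- Times 4, 8, 12 h: Σ(t − t̄)² = 32.
- Times 8, 12, 24 h: Σ(t − t̄)² = 138.67.

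| Times (h) | True t½ (h) | CV | SE (per h) | SE/ke | Non-positive slopes |
|---|---|---|---|---|---|
| 4, 8, 12 | 40 | 5% | 0.0088 | 51% | 2.5% |
| 4, 8, 12 | 40 | 10% | 0.0177 | 102% | 16% |
| 8, 12, 24 | 40 | 5% | 0.0042 | 25% | <0.1% |
| 8, 12, 24 | 40 | 10% | 0.0085 | 49% | 2% |
| 4, 8, 12 | 56.4 | 10% | 0.0177 | 144% | 24% |
| 8, 12, 24 | 56.4 | 10% | 0.0085 | 69% | 7% |

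In simulation at 40 h, the 4-8-12 h fit has a 5–95% range of 22–246 h at 5% error. The 8-12-24 h fit has 22–203 h at 10% error.

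**4. Possible bias from distribution.** Combine the 0.25 mg figures in section 4.1: AUC0-24 8,900 and AUC0-∞ 20,700 ng·h/L. The ratio is 0.43. A one-compartment decline would give 1 − 2^(−24/t½) = 0.32–0.36 for 42.8–37 h. The excess implies an early phase.

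Solve C(t) = A·e^(−αt) + B·e^(−βt) with three constraints: A + B = Cmax, A/α + B/β = 20,700, and the integral to 24 h equal to 8,900. At Cmax 1,130 ng/L and terminal 40 h this gives A = 820, B = 310 and a distribution half-life of 2.4 h. The error-free concentrations at 4, 8, 12 and 24 h are 545, 350, 277 and 205 ng/L.

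- Fit to 4-8-12 h: slope = ln(277/545)/8 = −0.085 per h, so t½ = 8.2 h.
- Fit to 8-12-24 h: slope = −0.0314 per h, so t½ = 22.1 h.

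Varying Cmax (919–1,130) and terminal half-life (37–42.8 h) gives 7.5–10.1 h and 17–26 h.

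The 3 µg/kg column tells a different story. There 8,570/35,800 = 0.24, against 1 − 2^(−24/56.4) = 0.26 for one compartment. No slow distribution phase shows in those AUCs.

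**5. Apparent route difference.** Take the same curve (Cmax 1,130, terminal 40 h) and add first-order absorption. The absorption half-life is assumed, since section 6.4 says no subcutaneous absorption data exist. The intravenous 4-8-12 h fit is 8.2 h.

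| Absorption half-life (h) | sc fit, 4-8-12 h |
|---|---|
| 0.35–1 | 7.2–7.5 h |
| 1.4 | about 8.5 h |
| 2 | 11.6 h |
| 3 | about 23 h |

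The routes look alike up to about 1.4 h and diverge from about 2 h. On 8-12-24 h, absorption half-lives of 0.35–1.4 h give 20.8–16.9 h against 22.1 h intravenously. That gap is small beside the standard errors in step 3.

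**The case against.** The best defence is that little depends on this number. Half-life is not primary. Bioavailability is the ratio of AUC0-t, so no ke extrapolation enters it. The washout is set from published data, and section 12.1 plans no test of half-life between routes. Section 6.4 is open that sampling targets absorption. All of this stands, and it lowers the severity.

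It can also be said that the rule for choosing ke points, and flags for profiles where it cannot be estimated, belong in a statistical analysis plan. That stands for the rule, but no rule can supply a terminal phase that was not sampled. The parameter, its level (subject and route) and the sampling window are all fixed in the protocol.

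Three stronger readings are tempting and are not supported:

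- **Sampling stops at 12 h.** It does not strictly: "If income permits 24 hours" adds a sample. At 10% error that cuts the relative standard error from 102% to 49%, which is better but still poor.
- **The reported half-life is bound to be several-fold too short.** The bias calculation joins AUCs from two different studies, and the 3 µg/kg column contradicts it. With an assumed A/B of 2 and a distribution half-life of 0.5 h or less, the 4-8-12 h slope still returns 38–40 h. In that case the failure is imprecision.
- **The routes will appear to differ in elimination.** A marked difference needs slow subcutaneous absorption, and the rate is unknown.

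**Conclusion.** The point holds: the schedule cannot support an elimination half-life per patient and route. The imprecision follows from the sampling times and the protocol's own 40 h, with only the 5–10% error assumed. The relative standard error of ke is 51–102% on the required late samples and 25–49% when 24 h replaces 4 h.

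Downward bias of intravenous values to about 7.5–10 h (4-8-12 h) or 17–26 h (8-12-24 h) is plausible but conditional on the two-study curve. A spurious route difference is possible, conditional on an absorption half-life of about 2 h or more. The mix of patients with and without a 24 h sample makes the values non-comparable whichever case is true.

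Severity: should be fixed. It does not threaten the primary parameters or the bioavailability ratio.

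**What to change.** In section 12.1, delete half-life and its formula from the parameters determined for each subject and route, and state that elimination half-life is not estimable from sampling over 0–12 h, or 24 h where available.

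If a value is still wanted, label it an apparent half-life over the sampled window. State which time points give ke, report patients with and without the 24 h sample separately, and say that it is neither interpreted as elimination nor compared between routes.

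The cost is one short edit. A secondary descriptive number is lost or relabelled. No sample or visit changes, and Cmax, tmax, AUC0-t and the bioavailability ratio are unaffected.
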